### Objectives and hypotheses

The main objective of this randomized controlled trial (RCT) is to investigate the synergetic effects of a group-based multidomain training program that combines cognitive video-game training with physical exercise, in comparison to those produced by cognitive training combined with physical control activity, physical training combined with cognitive control activity, or a combination of both control activities, on behavioral and electrophysiological measures of executive control (set-shifting, response inhibition, and information updating and monitoring) and memory functions (immediate and delayed visual and verbal memory). These cognitive functions, which are often compromised in later years, are essential for everyday activities. The second objective is to investigate whether event-related potential (ERP) latencies of the P2 component are shorter and N2 and P3b components assessed in a memory-based task-switching task are enhanced after training. Electrophysiology provides a very useful online measure to identify the contribution of different processing stages of executive functioning. ERPs can help us to understand the specific executive control impairments occurring with age, as well as the possible effects of the different types of intervention investigated in this RCT. To this end, the task-switching paradigm is a valid task that helps to identify the cognitive processes that most decline with ageing [75]. However, electrophysiological studies conducted to evaluate training-related effects in older adults using this task are scarce [76]. Finally, we are interested in finding out whether possible enhancements persist after a 3-month period without training.

We expect to find greater behavioral improvements in executive control and memory functions after training, larger maintenance effects, and shorter ERP latencies of the P2 component and enhanced N2 and P3b components in the multidomain training condition in comparison to both single-domain conditions. We also expect the multidomain group and both single-domain groups to outperform the active control group at the 3-month follow-up period.

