### Sample size

We conducted an a priori power analysis using G*Power 3.1 [80] to calculate the appropriate sample size. Using an α value of 0.05, power of 0.80, and a medium effect size (*f* = 0.38) for video-game training [45] and physical training [81], and four groups within the *F*-test family, a total sample size of 124 is required. Considering a dropout rate of 12%, a total of 144 participants would be sufficient to detect significant main effects. According to this calculation, the adequate number of participants in each group (multidomain training, video-game training, physical activity training, and active control) is 36. According to this, we will set a sample size of 36 participants per arm, which is adequate for the experimental design. According to Montgomery et al. [82], with this number of participants the design would be underpowered to detect an interaction effect, as it would need a fourfold increase in sample size. However, given that lower interaction effects would not be clinically relevant, we decided to maintain our initial sample size estimation.

In the elaboration of this protocol, we have followed the SPIRIT 2013 explanation and elaboration guidance for reporting protocols of clinical trials [83].

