### General procedure

After baseline, participants who meet the inclusion criteria will be randomly assigned to one of the four groups. The active control group was introduced in the design to control for placebo effects [84]. The main question is whether the multidomain group will outperform the single-domain groups at posttest, and whether these groups will outperform the active control group in a series of cognitive-control and memory tasks (see below). We focused on these cognitive domains because they deteriorate with age and are critical for independent living.

All methodological designs of primary and secondary outcomes are constructed using the rules of counterbalance and stimulus rotation. Response keys will be counterbalanced across conditions. The computerized tasks have been programmed with E-Prime 2.0 (Psychological Software Tools Inc.). Continuous EEG activity will be recorded in our laboratories with thin electrodes from 40 scalp sites using NuAmps amplifiers while participants perform the task-switching task.

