### Statistical analysis

All data from participants with complete baseline assessment and who attended at least one training session will enter into a primary intention-to-treat analysis. For the secondary per-protocol analysis, only the data of participants with a complete cognitive assessment and an attendance rate ≥ 70% will be considered.

Executive functions (set shifting, maintenance, inhibitory control) and memory functions (short-term, visual, and verbal immediate and delayed memory) will be assessed at pretest, posttest, and follow-up. The statistical analysis corresponding to the behavioral results will be carried out with the SPSS statistical package for Windows (SPSS 25.0; IBM Corporation). Results will be considered significant at *p* < 0.05, with Bonferroni-corrected post hoc tests performed as appropriate. We will explore the missing data to ascertain their pattern and will apply an adequate technique of multiple imputation. Repeated ANOVA measures will be conducted with four groups (multidomain training, cognitive training, exercise training, active control) at three time points (pretest, posttest, follow-up) to test the primary hypothesis (i.e., differences in efficacy between interventions compared to the active control condition). Repeated ANOVA measures will also be performed to determine the effect of the interventions on secondary outcomes. To evaluate the effect size of the combined multimodal group versus each individual intervention group and the control arm, we will use multimodal regression with an interaction term. Electrophysiological data will be analyzed with CURRY 8.0.2, the EEGLAB toolbox [92], and the ERPLAB plugin for EEGLAB [98].

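### The trial's main question (synergy, and combined versus single training) is neither the named primary test nor powered, and the relevance argument for accepting this conflicts with the protocol's own effect size

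*Protocol article*

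**What the plan says.** All references are to the Protocol article.

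- **Objectives and hypotheses**: "The main objective of this randomized controlled trial (RCT) is to investigate the synergetic effects of a group-based multidomain training program". The hypothesis is that the combined arm improves more than both single-domain arms.
- **General procedure**: "The main question is whether the multidomain group will outperform the single-domain groups at posttest". The sentence goes on to ask whether these groups also do better than active control.
- **Sample size**: "Using an α value of 0.05, power of 0.80, and a medium effect size" (f = 0.38, given for video-game training and for physical training), with "four groups within the *F*-test family, a total sample size of 124 is required". After 12% dropout, "a total of 144 participants would be sufficient to detect significant main effects". The section then concedes that the design is underpowered for an interaction, which would need four times the sample, and accepts this: "given that lower interaction effects would not be clinically relevant, we decided to maintain our initial sample size estimation".
- **Statistical analysis**: a repeated-measures ANOVA with four groups and three time points tests the primary hypothesis, glossed as "differences in efficacy between interventions compared to the active control condition". Bonferroni post hoc tests are to be made where appropriate. A regression with an interaction term is planned to evaluate the effect size of the combined arm against each other arm.

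**The concern.** Two different questions are presented as the main one. Synergy is the CI x EI interaction: does the combination give more than the sum of its parts? Combined versus single training is a pair of simple comparisons, and if the effects merely add up, the combined arm wins both with zero synergy. The primary test targets neither question, and the sample size covers neither.

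The reason given for tolerating low interaction power is a claim about clinical relevance. If the interactions likely to be missed are as large as the training effects the trial was sized to find, that claim fails. The sentence would also give cover to reading a non-significant interaction as absence of a relevant synergy.

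**Working it through.** **Inputs.** From the Sample size section: f = 0.38, alpha 0.05 (taken as two-sided), power 0.80, four equal arms, 124 evaluable (31 per arm), 144 randomised (36 per arm). The protocol gives no SD and no pre-post correlation, so effects are in SD units of the analysed score (one score per participant).

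**1. The plan's own figures.** The dropout step reproduces: 31/0.88 = 35.2, rounded up to 36, and 4 x 36 = 144. The 124 does not. A one-way four-group F test with f = 0.38 (noncentrality f²N, df 3 and N - 4) reaches power 0.80 at N = 80, and 124 corresponds to power 0.95. That is a separate matter, and the powers below use the stated arm sizes. The fourfold statement is consistent: with n per arm, a factorial main effect has SE 1/√n and the interaction (a difference of differences) has SE 2/√n. An interaction equal in size to a main effect therefore needs four times the sample.

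**2. What f = 0.38 means.** The protocol does not say, so both readings are carried.
- *Omnibus effect with additive arms.* Means 0, d, d, 2d have SD d√0.5, so d = 0.38/0.707 = 0.54 SD per component.
- *Effect of one two-level factor.* d = 2f = 0.76 SD.

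**3. What the omnibus F can tell.** Its power depends only on the spread of the arm means.
- Additive, no synergy: 0, 0.54, 0.54, 1.07 SD; f = 0.38.
- No advantage of the combined arm: 0, 0.88, 0.88, 0.88 SD. The SD of the means is 0.433 x 0.88 = 0.38, so f = 0.38.

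Power is 0.95 at N = 124 and 0.98 at N = 144 in both cases. A significant result is equally likely whether the combined arm beats the single arms or merely ties with them. The group-by-time F in the planned ANOVA is likewise an omnibus test and shares this limit.

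**4. Synergy.** SE = 2/√31 = 0.359, or 2/√36 = 0.333. Noncentral t with df = 4n - 4:

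| | 31 per arm | 36 per arm |
|---|---|---|
| Detectable with 80% power | 1.01 SD | 0.94 SD |
| Power, synergy 0.54 SD | 0.32 | 0.36 |
| Power, synergy 0.76 SD | 0.56 | 0.62 |

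**5. Combined versus one single arm.** SE = √(2/n), same df:

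| | 31 per arm | 36 per arm |
|---|---|---|
| 0.54 SD, unadjusted | 0.55 | 0.62 |
| 0.54 SD, Bonferroni over two | 0.44 | 0.51 |
| 0.76 SD, unadjusted | 0.84 | 0.89 |
| 0.76 SD, Bonferroni over two | 0.76 | 0.83 |

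The protocol does not state the size of the Bonferroni family. Over all six pairs, power falls to 0.29-0.35 and 0.62-0.71.

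**6. Sensitivity to scale.** If f refers to raw-score SDs and the analysed score is change, the detectable synergy is multiplied by √(2(1 - ρ)). This gives 0.84-0.91 SD at ρ = 0.6 and 0.73-0.79 SD at ρ = 0.7. With pretest as covariate the factor is √(1 - ρ²) = 0.8 at ρ = 0.6, which gives 0.75-0.81 SD. These correlations are assumptions.

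**The case against.** The strongest reply is that the plan is more open and more complete than the criticism allows. Much of it stands.

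- *A reader might infer that the plan has no route to its main question.* It has two: Bonferroni post hoc tests and a regression with an interaction term. What remains is that neither is the named primary test, neither was powered, and the regression is named only for effect size.
- *A reader might infer a flat contradiction between General procedure and Statistical analysis.* The General procedure sentence also asks about active control, so the stated primary hypothesis covers part of the main question. The alignment is incomplete rather than absent.
- *A reader might infer that baseline is discarded, or that the sample size rests on a group effect diluted by averaging in the pretest.* The documents do not support either. The behavioural primary outcomes are specified as change from baseline, and the main effects in the Sample size section read naturally as the effects of the two trainings. Covariate adjustment is simply more efficient: its variance relative to change scores is (1 + ρ)/2, a reduction of 15-25% for ρ from 0.7 to 0.5.
- *A reader might infer that the combined-versus-single comparisons are badly underpowered.* That depends on the reading of f. At 0.76 SD the unadjusted comparison has adequate power.
- *A reader might infer that the investigators will report a null interaction as no synergy.* Nothing in the protocol says so, and low interaction power is admitted.

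Admitting low power does not, however, repair the reason given for accepting it.

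**Conclusion.** The point holds in this form. The main objective (synergy) and the leading half of the main question (combined versus single training) are not what the named primary test addresses, and the sample size was set for neither. The relevance argument has no threshold behind it and conflicts with the protocol's own effect size: a synergy as large as the whole assumed training effect would be missed 64-68% of the time at 0.54 SD and 38-44% at 0.76 SD.

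These figures assume one score per participant in analysed-score SD units, 31 to 36 per arm, and a two-sided 5% test. A reader might go further and say that the detectable synergy exceeds any training effect the plan assumes, whatever the scale. It does in analysed-score units. In raw-score units with a high pre-post correlation it comes down to about the 0.76 SD reading. Even then, smaller synergies have less than 80% power, and nothing in the protocol shows that they are irrelevant.

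**What to change.** 1. In Statistical analysis, reword the primary hypothesis to match Objectives and hypotheses and General procedure, keeping synergy and combined-versus-single as two separate questions.
2. For each outcome, fit a baseline-adjusted model with pretest as covariate and CI (yes/no), EI (yes/no) and CI x EI as factors. Pre-specify CI+EI versus CI+EC and CI+EI versus EI+CC at posttest as the primary contrasts, with a stated alpha rule (for example Bonferroni over the two). Keep the comparisons with active control as further contrasts.
3. Report CI x EI separately as the synergy estimate with a 95% confidence interval, and say that a non-significant result does not exclude a relevant synergy.
4. Delete the sentence on clinical relevance. State the detectable synergy as a range: about 0.94-1.0 SD unadjusted, and about 0.8 SD in raw-score units with baseline adjustment if the pre-post correlation is 0.6 (an assumption).

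The cost is protocol wording and a standard linear model in the software already planned, with no new participants or data. The downside is a more modest synergy claim. Covariate adjustment improves the power of the two primary contrasts, but does not guarantee 80% under the smaller reading of f, and the protocol should say so.

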### Recruitment

Participants will be recruited through organized information sessions about the project at senior programs at universities and through radio advertisements.

### Randomization and blinding

After the baseline assessments, participants will be randomly allocated to one of the four training protocols in a stratified process using the online tool Random Lists (move this to the other linehttps://www.randomlists.com/). [name] will generate the random sequence and will assign participants to interventions. At first, participants who came in couples will be randomly allocated as a unit to one of the four groups, and afterward the same procedure will be performed with the individual participants. This procedure aims to minimize dropouts due to separating couples in different groups. Participants and exercise instructors will be blinded to treatment allocation (single-blind). Data analysis will not be blinded, as it will be performed by the investigators who actively collaborate in the study. We do not envision any reason why participants should be unblinded, either during the trial or at the end of the study.

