### Trial setting

This study will be conducted in Madrid (Spain) at the UNED Psychology building. The screening, pretest, posttest, and follow-up assessments will be conducted in our laboratories at the Psychology building. The training sessions of the four groups will be conducted in three waves in spaces specifically equipped and prepared for this purpose at our university site as well as at a city council facility.

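### The stated model has only arm and time; the randomisation stratum and the training wave should be added, with time interactions and together with an allowance for training-group and couple clustering

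*Protocol article*

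**What the plan says.** Under Randomization and blinding, "participants will be randomly allocated to one of the four training protocols in a stratified process". No stratification factor is named. The only structure described is an order: people who enrol as a couple are allocated together, as one unit, and single participants follow.

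Under Trial setting, "The training sessions of the four groups will be conducted in three waves". Study design puts 10 to 12 people in a training group. Sample size sets 36 per arm.

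Study design describes a 4 × 3 mixed design with arm between subjects and time within subjects. Statistical analysis repeats it: "Repeated ANOVA measures will be conducted with four groups" at three time points. No stratum or wave term is stated. The only covariates mentioned are motivation and engagement, in secondary analyses (Objectives and hypotheses). The outcome sections specify change from baseline as the metric.

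**The concern.** A factor that is balanced across arms, is related to the outcome and is left out of the model adds its variation to the residual but not to the arm contrast. The test is then conservative and loses power. Stratum and wave are both candidates.

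The article gives reasons why waves might differ even in change over time. Recruitment spans about a year, so waves may fall in different seasons. Allocation takes place 1 to 8 weeks after baseline, so the gap from baseline to training can vary. At stake is some precision in every between-arm comparison, in a trial that the Sample size section already describes as underpowered for an interaction.

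**Working it through.** **Inputs from the article.** α = 0.05, power 0.80, f = 0.38, four groups, N = 124 before dropout and 144 after; 36 per arm; three waves; training groups of 10 to 12. With 36 / 3 = 12 people per arm per wave, there is about one training group per arm per wave.

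**Assumed.** The share R² of the relevant error variance due to stratum or wave is not given; the range used is 0 to 20%. Waves are taken as balanced within arm.

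**The plan's own figure.** The article says that "a total sample size of 124 is required". With f = 0.38, a one-way F test needs 80. The value 124 is obtained with f = 0.25, a between-factor repeated-measures test, three measurements and correlation 0.5 (power 0.814). Dropout: 124 / 0.88 = 141, close to 144. This mismatch is a separate matter. Only N = 124 is carried forward, with the effect set to give about 80% power.

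**1. Between-subject arm effect.** Adjusted noncentrality is λ = f²N / (1 − R²), with 3 and 124 − 7 = 117 df (two df for wave, one for stratum). Unadjusted power is 0.80 at f = 0.301.

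| R² | adjusted power, f = 0.301 | adjusted power, f = 0.38 (unadjusted 0.952) |
|---|---|---|
| 0 | 0.80 | 0.952 |
| 1% | 0.804 | 0.954 |
| 2% | 0.808 | 0.956 |
| 5% | 0.82 | 0.961 |
| 10% | 0.84 | 0.970 |
| 20% | 0.89 | 0.984 |

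**2. Arm-by-time test, stable differences.** If wave w shifts both pretest and posttest by the same amount a(w), change = (post + a(w)) − (pre + a(w)) = post − pre. The shift cancels. In 40,000 simulated trials with a 20% stable wave share, power was 0.81 with and without wave, and type I error was 0.05 for both.

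**3. Arm-by-time test, differences in change.** Here the wave shift stays in the change score. With balance, the unadjusted error mean square is inflated by 1 / (1 − R²) while the arm mean square is not. The test then behaves as if its critical value, 2.68 on 3 and 120 df, were divided by (1 − R²). At 20% that is 2.68 / 0.80 = 3.35. With f = 0.303, λ = 0.303² × 124 = 11.38. Simulation results, with the closed form in brackets:

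| R² | power, no wave | power, with wave | type I error, no wave |
|---|---|---|---|
| 5% | 0.780 (0.783) | 0.803 (0.804) | 0.040 (0.042) |
| 10% | 0.757 (0.757) | 0.807 (0.804) | 0.033 (0.034) |
| 20% | 0.693 (0.695) | 0.805 (0.804) | 0.020 (0.021) |

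The gains are about 2, 5 and 11 points. At 2% the closed form gives 0.796 against 0.804, under one point.

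**4. Training-group correlation.** Assume 3 waves × 4 arms × 12 people, residual SD 1 and training-group SD 0.15 (not in the article). The expected arm mean square under no arm effect is 1 + 12 × 0.0225 = 1.27.

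- Error without wave, waves equal: (8 × 1.27 + 132) / 140 = 1.015.
- Each wave SD s adds 96s² / 140. At s = 0.4 the error is 1.125.
- Error with wave in the model: (6 × 1.27 + 132) / 138 = 1.012.

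Scaling the critical value by error / 1.27 gives type I error 9.9% (s = 0), 9.2% (0.2), 8.4% (0.3) and 7.4% (0.4) without wave, and 10.0% with wave. Simulations agree: about 7 to 10% without wave and about 10% with it. The arm-and-time model is too liberal throughout, and a wave term alone moves it slightly further that way.

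**5. Analysis of 12 training-group means.** Adding wave moves the test from 3 and 8 df (critical value 4.07) to 3 and 6 df (4.76). With group SD 0.15 and arm steps of 0.4 SD, 20,000 simulations gave power without and with wave of 49% and 43% if waves do not differ, 34% and 42% at wave SD 0.2, and 25% and 43% at 0.3.

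**The case against.** The strongest objection is that a journal article condenses the plan. Naming the ANOVA's main factors does not exclude others, and an adjustment list may sit in a document not shown. That is fair, and it is why this is a recommended addition and not an error. It does not remove the point: the article does state a design and a model, and that model has only arm and time.

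Three stronger readings are tempting, and the article does not support them.

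- *Allocation was restricted by wave and the analysis ignores it.* Wave appears only as a feature of how training is delivered. Nothing says that it was a stratum. That it is crossed with arm is an inference from the group size and the number per arm. Couple versus individual is likewise a reading of the order of allocation, whose stated aim is to limit dropout.
- *All stratum and wave variation costs power in the main test.* The planned metric is change from baseline, so stable differences cancel from the arm-by-time error. They stay only in the error of the arm main effect.
- *The standard error is simply too large.* This holds only if there is no correlation within training groups and couples. Even a modest group SD of 0.15 reverses the net direction.

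It can also be said that the gain is small at the stated effect. At f = 0.38, power at N = 124 is already 0.952, and adjustment adds about 3 points at most over the range. That stands for the omnibus arm test.

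**Conclusion.** The point holds as a modest, inexpensive improvement. The article describes stratified allocation and three waves, and its stated model uses neither. The power gain from adjustment is about 0 to 9 points for the between-subject arm effect. For the arm-by-time test it is nil if strata or waves differ only in stable level, and about 2 to 11 points if 5 to 20% of the variance of change is due to wave. At 1 to 2% it is under one point.

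Every variance share is assumed, waves are taken as balanced across arms, and the power figures ignore clustering. A reader might conclude that the planned test is conservative overall. That does not follow, because correlation within training groups and couples pushes the error rate up, and the article gives nothing from which to judge the net effect.

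**What to change.** - In Randomization and blinding, name the stratification factor or factors.
- In Statistical analysis, add the randomisation stratum (couple or individual, plus any other stratum used) and wave as fixed factors in the between-arm models. Give each its interaction with time, or enter them as factors in a model for change from baseline.
- In the same step, allow for correlation within training groups and couples. Adding wave without this leaves the test too liberal.

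The change takes a few lines of text. At participant level it uses about three degrees of freedom out of about 120, which is negligible. In a training-group-level analysis it can lose a few points of power if waves do not differ (49% to 43% in the assumed setting), and it gains when they do.

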### Participants

Participants will be male and female, healthy, and independently living volunteers aged between 60 and 80 years. Those who complete the baseline assessments and meet the inclusion criteria (see later) will be randomly assigned to one of the four intervention conditions. The timing of group allocation will take place between 1 and 8 weeks after baseline.

Participants may discontinue their intervention for personal or medical reasons. To minimize dropouts and improve adherence to the intervention, four face-to-face adherence reminder sessions will take place during the training program emphasizing the importance of training compliance. Furthermore, to increase participant retention and to reduce loss to follow-up, all participants will receive a personalized report of their performance and training progress at the end of the study. Participants will receive a small refund in compensation for their travelling expenses.

Even though this trial is low risk, participants might harm themselves during the practice of physical exercise. To minimize the risk of injuries, each participant will be carefully monitored during the training sessions. The interventions will be designed in collaboration with the exercise instructors, after a detailed analysis and taking into account each participant’s possible medical issues. Spontaneously reported adverse events or other unintended effects will be registered and analyzed, and if necessary the protocol will be modified to eliminate the causing element. We have signed an insurance policy in case any participant suffers harm during the physical training.

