### Data monitoring committee and data management

Personal information about participants obtained during the individual interviews as well as performance data and all study-related information will be coded in a database and stored securely at the study site to maintain participant confidentiality. A coded identification (ID) number to maintain participant confidentiality will identify all data collection and administrative forms. The electronic data will be stored securely on a university computer and a high-drive disc (HDD) that are password protected. Paper copies as well as HDDs will be securely stored in a locked cabinet at the study site. All forms, lists, appointment records, consent forms, and any other listings that link participant ID numbers to other identification information will be stored in a separate, locked file in a limited access area. Only the members of the researcher team directly involved in data collection, maintenance, and management will have access to the data set.

The data monitoring committee (DMC) will be composed of [name] and [name], who will regularly check on the correctness of data collection and encoding and its correspondence with the entrances in the laboratory diary. The DMC will be responsible for securing the data on a weekly basis on the aforementioned devices. The data will be stored securely in our laboratory for 5 years.

We have not planned to conduct subgroups of interim analyses.

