### Steering committee

The steering committee will meet at least on a quarterly basis to monitor the trial processes, independently of the funding organization. The committee will check compliance with the assessment and training protocols and the timelines, and will oversee and manage the trial. Its members, who form an active part of the research group, are SB and [name]. They will verify trial processes, such as participant enrollment, informed consent, eligibility, allocation of participants to groups, and adherence to trial interventions.

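### One person both generates the random sequence and assigns participants, so allocation is not concealed from whoever applies it

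*Protocol article*

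**What the plan says.** All references are to the protocol article.

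- **Roles (Randomization and blinding).** One removed name is the subject of both verbs: that person "will generate the random sequence and will assign participants to interventions". Where two people share a task, as in the section on the data monitoring committee, two removed names appear.
- **Timing and tool.** "After the baseline assessments, participants will be randomly allocated to one of the four training protocols in a stratified process using the online tool Random" (the quotation breaks off within the tool's name). The Participants section adds: "The timing of group allocation will take place between 1 and 8 weeks after baseline".
- **Two passes.** The section says that "participants who came in couples will be randomly allocated as a unit to one of the four groups, and afterward the same procedure will be" applied to individual participants. The stated reason is to avoid dropouts caused by separating couples.
- **Blinding.** "Participants and exercise instructors will be blinded to treatment allocation (single-blind"). On analysis: "Data analysis will not be blinded, as it will be performed by the investigators who actively collaborate in the study".
- **Oversight (Steering committee).** The committee verifies, among other processes, the allocation of participants to groups. Its members are described as active members of the research group.
- **Existing coding (Data monitoring committee and data management).** "A coded identification (ID) number to maintain participant confidentiality will identify all data collection and administrative forms".

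**The concern.** Randomisation protects a comparison between arms only if the person placing participants can neither foresee the result nor redo it. Here the protocol fixes the opposite arrangement: the maker of the list is also its user. This is a stated division of work. A fuller analysis plan could not repair it without changing what is written.

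What is at stake is limited but real. Participants are already enrolled and tested when they are allocated, so the risk is not selective enrolment. It is that enrolled people are moved between arms on something that predicts how much they will gain. The protocol itself treats motivation and engagement as possible sources of variation in the primary outcomes (Objectives and hypotheses) and plans to use them as covariates in secondary analyses.

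**Working it through.** The plan gives no figure on this point, so the check is mainly a comparison of the sections, followed by one calculation on size.

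**1. Does the stated procedure conceal allocation from the assigner?** The article does not say whether the sequence is drawn before the roster is matched to it or in the same act. Both cases lead to the same place:

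- If it is drawn beforehand, the assigner knows each coming allocation when matching a name to it.
- If it is drawn on the roster itself, the assigner sees the outcome while it can still be replaced by another draw.

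In neither case does a stated step stand between generating and applying the sequence.

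**2. What is known by then?** Allocation comes 1 to 8 weeks after baseline. Training runs in three waves (Trial setting) in groups of 10–12 (Study design), with 36 participants per arm (Sample size). If the waves are equal, which is an assumption, 36 / 3 = 12 per arm per wave. Each wave is then placed from a known roster into classes of known size. Because couples go first, the filling of the classes is visible before individuals are placed.

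**3. What check is described?** Only the steering committee's verification, by members of the same research group. The article mentions no reproducible record that they could verify against.

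**4. Can a size be attached?** Take an illustration with assumed numbers: 4 of 36 participants in one arm are 1 SD better than the average ones they replace, and the mirror image occurs in a comparator arm.

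- Shift in one arm's raw mean: 4/36 = 0.11 SD.
- Shift in the raw contrast: 2 × 4/36 = 0.22 SD.

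The behavioural primary outcomes, however, are specified as change from baseline (Primary outcomes) and analysed over three time points (Statistical analysis). The effect on the change contrast depends on how the participants were chosen:

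- *Stable difference in level.* The same 0.22 SD is present at pretest and posttest, so the change contrast moves by 0.22 − 0.22 = 0.
- *Selection on the observed baseline score.* With an assumed pre–post correlation r and equal SDs at both times, the posttest shift is r × 0.22, so the change contrast moves by 0.22 × (r − 1):

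| Assumed r | Shift in change contrast |
|---|---|
| 0.5 | −0.11 SD |
| 0.7 | −0.07 SD |
| 0.9 | −0.02 SD |

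  The sign is against the arm that received the better scorers.
- *Selection on expected gain or motivation.* This would bias the change contrast directly, but the documents give no input from which to size it.

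The raw-mean figures therefore do not carry over to this trial's metric, and no single bias figure can be supported.

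**The case against.** The strongest case on the other side has five parts.

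- **Enrolment and baseline testing come before allocation.** Foreknowledge cannot affect who enters or how they are tested at baseline, and those are the usual main harms of poor concealment. This stands, and it narrows the point to movement between arms.
- **Each pass is itself random, and the process is called stratified.** Seeing how classes fill matters only if the random result is then set aside. This also stands. The concern is that nothing stated prevents that, not that the passes are faulty.
- **The assigner's knowledge is not documented.** The article says only that allocation follows baseline. It does not say that this person sees scores, recruits, screens or tests. A reader might infer that allocation was made with scores in hand, or that lists were redrawn. The documents support neither.
- **Testers.** A reader might also infer that those who test participants know the allocation, because only participants and instructors are listed as blinded. That is silence in a condensed article. It is also a separate matter from concealment, and it would bear less on the task-switching, N-back and Stroop tasks, which are computerised.
- **Concealment mechanics are often left to the full protocol.** That is fair for sequence storage and redraw rules. It does not apply to the combination of the two roles, which the article states.

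It is also fair to note that the steering committee does verify allocation, and that belonging to the research group does not make its check worthless. The check would be worth more if it had a reproducible draw to work from.

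**Conclusion.** The point holds in a limited form. The protocol assigns generation and assignment to one person, so allocation is not concealed from the person applying it. Steering of enrolled participants between arms is not prevented by the procedure as stated. This rests on reading the single removed name as one person, which the sentence structure supports.

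It is a risk, with no evidence that it materialised. A reader might take 0.11 or 0.22 SD as the bias in the trial's results. That is not supported: those values concern raw means under invented numbers. On the change metric, the same illustration gives roughly zero, or −0.02 to −0.11 SD for assumed correlations of 0.9 to 0.5. Only steering on expected gain would favour an arm on that metric, and its size is unknown. The change is worth making because it is cheap and removes the doubt, not because a large bias has been shown.

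**What to change.** Amend Randomization and blinding as follows.

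1. **Waves not yet allocated.** Draw each wave's allocation once, by a script with a seed recorded beforehand. Run it on coded IDs only, in a fixed order. Flag each couple as one unit, and place couples and individuals in the same run under the planned stratification. Allow no redraws, and archive the script, seed and output so that the steering committee can rerun the draw.
2. **Who runs it.** An existing team member who does not recruit, screen or test. If the present assigner already meets this description, say so.
3. **Waves already allocated.** Recruitment began in February 2019 and the trial is described as ongoing (Trial status), so some waves may be past changing. For these, document how the list was drawn and whether it was redrawn.
4. **Where existing staffing allows,** withhold the allocation from those who give the examiner-administered tests (TMT, WMS-III) at posttest and follow-up.

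The cost is a short script, a small change of roles and some constraint on who tests whom. No extra participants or visits are needed, and couples still stay together. The drawback is that an unlucky draw cannot be repeated.
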